### Outcomes and data collection

Using the study website, the eligible participants will provide demographic data and will complete the outcome scales at the baseline and post-intervention. More specifically, demographic data will include gender, age, years of PHN experience, job title, educational background, affiliation, previous experience with local healthcare planning education at the undergraduate level and on-the-job training after graduation, previous experience with local healthcare planning, whether they worked with colleagues who played active roles in healthcare planning, and information on promoting the daily practices of PHNs. To decrease the number of dropouts, we will send e-mails to all participants with information about the study progress and will remind them to answer the post-test questions. At the baseline and post-intervention, the participants will address the following outcomes.

#### Competencies related to involvement in health policy

The primary outcome will be measured using a self-reported 16-item scale targeting PHN competencies in public health policy in the context of Japanese local governments [33]. The scale was confirmed as reliable and valid for use in Japan and is only available in Japanese. The first eight items measure community partnership among PHNs when developing health policy, while the remaining items evaluate competencies related to the community nursing diagnosis cycle. All items will be measured using a 4-point Likert scale, ranging from 0 to 3: 0 (unable to do), 1 (partially unable to do), 2 (partially able to do), and 3 (able to do).

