## Abstract

**Background:**

Promoting of local healthcare planning is crucial for assisting public health nurses in improving community health inequities. However, there is no effective educational program for developing relevant skills and knowledge among these nurses. Therefore, this study aims to assess the feasibility of a newly developed web-based self-learning program to promote the involvement of public health nurses in the local healthcare planning process.

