In Japan, approximately 60% of PHNs work for prefectural or municipal governments [20]. The national practice guidelines for PHNs published in 2013 increased their expected involvement in local healthcare planning [7]. Undergraduate curricula began to include these skills in 2007 [21], and the national PHN examination added related requirements in 2017 [22]. However, approximately 50% receive continued education relevant to local healthcare planning [23, 24]. Previous studies have not investigated whether PHNs who focused on self-directed learning improved self-confidence, competency, and readiness [25, 26].

Japan is facing a falling birth rate and an aging population. Consequently, local governments are promoting the reduction of public service positions despite the necessity of needs-oriented local healthcare plans [27]. The COVID-19 pandemic has also accelerated the growing shortage of PHNs [28], which emphasizes the need for effective and efficient educational programs targeted at improving competencies related to local healthcare planning. Thus, a web-based learning program would help PHNs understand theoretical concepts and practical strategies that are relevant to the healthcare planning process whenever they want without the need to contact other participants. Subsequently, this study will verify the effects/feasibility of a user-friendly web-based self-learning program designed to improve competencies for PHNs who are involved in the local healthcare planning process. Further, the study will verify the program outcomes and data collection methods using relevant scales and examine the preliminary effects of the web-based self-learning program, thus providing relevant data for calculating the sample size needed to conduct a future definitive RCT.

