### Assessment of the trial feasibility

We will assess the feasibility of this study based on the recruitment rate, dropout rate, and data completion rate. We will set the corresponding criteria to assess the success of feasibility; the recruitment rate will be 2.4%, the dropout rate, and the data completion rate will be 50% based on the previous pilot study [12]. We also will ask the participants for their feedback on the feasibility of the trial and web-based learning self-learning program, clarifying areas that need improvement and/or continual refinement as open-ended survey questions.

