### Statistical analysis

We will conduct descriptive statistics (e.g., recruitment rate, dropout rate, and data completion rate) to assess the feasibility of this study and analyze intergroup baseline differences in the data and primary outcomes using the Mann-Whitney *U*-test and the chi-square/Fisher exact test. We will assess whether previous experience in local healthcare planning and other factors affected the study outcomes based on the results of the Mann-Whitney *U*-test and the chi-square/Fisher exact test. Analyses will be performed according to the intention-to-treat principle. We will use IBM SPSS for Windows (version 25; IBM Corp, Armonk, NY, USA) for the analysis and *p*-values < .05 indicating statistically significant intergroup differences. This study is expected to have a power ≥.80 and α ≤.05, assuming a medium effect size (*d* = .30) [35].

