## Discussion

This pilot RCT will aim to confirm the feasibility and preliminary effects of a web-based self-learning program designed to increase the involvement of PHNs in local healthcare planning by enhancing relevant competencies. We will also examine the eligibility of the implemented outcome scales and data collection procedures in preparation for a future definitive RCT. The strengths of the novel self-learning program are as follows: (1) user-friendly web-based educational program, (2) eligible participants will be selected based on clear criteria, (3) all participants will be given equal opportunities to learn about local healthcare planning through the program (i.e., after we collect data from the intervention group), and (4) primary outcomes will be measured using validated standardized scales. This study also has the strength that PHNs will understand theoretical concepts and practical strategies relevant to healthcare planning without contact with other participants due to the COVID-19 pandemic.

We developed the abovementioned program based on several components, including adult learning theory [31], a nationwide survey [25], and previous related studies [5, 16, 17, 21, 23, 25]. Through participation in web-based self-learning modules, the participants can acquire the competencies of local healthcare planning and bridge the gaps between the community health needs that PHNs must address in daily practice and the context of newly developed local healthcare plans. The development of local healthcare planning can improve health inequities by bridging the gaps in community health needs [6]. In this regard, PHNs are responsible for enhancing health equity and developing needs-oriented health policy through their practices [4, 5]. This pilot feasibility study will also adopt validated outcome scales, which will be used to gather the preliminary data needed to calculate an appropriate sample size for a future large-scale RCT. Owing to the constraints of the COVID-19 pandemic, we will also ensure that participants are socially distanced to prevent infection. More specifically, our web-based learning modules do not require participants to make direct contact with one another and will also eliminate travel time.

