As mentioned, participants in the control group can access the same learning program in the post-intervention context, providing them with critical education while minimizing the number of dropouts and ensuring educational equality. Further, we will assess whether previous experience with local healthcare planning impacts the study outcomes. These results will be used to revise different aspects of the program and the inclusion criteria for a future definitive RCT.

We have also identified some potential limitations. First, the pilot study only included a small sample from one prefecture in Japan. In this regard, the participants will be likely to have strong interests in the nature of the study program, thus increasing their motivation to engage in continued education. This may result in selection bias and influence the distribution of data. However, this study will focus on the feasibility of the program, not its effectiveness. Regardless, these issues should be carefully considered when interpreting the data.

Second, we will protect the privacy of all participants by anonymizing the data and did not collect the names of the local governments where they are employed. As such, we cannot rule out the possibility that eligible participants from the same local governments will be allocated to different study groups. In this regard, we cannot entirely prevent contamination or instances in which the program content is leaked from the intervention group to the wait-listed control group. We will explain this issue to all participants and repeatedly ask the intervention group to keep the program contents confidential.

Third, we could not control some confounding factors, such as the provenance area of participants and rural versus urban areas and the lack of follow-up assessment in this study. Fourth, only five PHNs confirmed the web-based self-learning modules due to the COVID-19 pandemic. Fifth, the reliability and validity of the Japanese version of Fisher’s Self-Directed Learning Readiness Scale has not been confirmed. Thus, we could not use this scale in this study.

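### The trial's aim is stated inconsistently, and its primary outcome is a competency scale tested at p<.05 that 14 nurses cannot inform, while the feasibility criteria have no outcome rank

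*Protocol article*

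**What the plan says.** All references are to the protocol article.

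**Aim.** The abstract's Background says "this study aims to assess the feasibility of a newly developed web-based self-learning program". The limitations in the Discussion say "this study will focus on the feasibility of the program, not its effectiveness", and the Conclusions again give feasibility as what the trial will determine. The Background, however, says "this study will verify the effects/feasibility of a user-friendly web-based self-learning program", and the Discussion opens with "This pilot RCT will aim to confirm the feasibility and preliminary effects of a web-based self-learning program". The short section on preliminary effects expects improvement on all three outcome scales. The end of the Discussion promises to check whether participants' competencies improve.

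**Outcomes.** In the section on competencies, "The primary outcome will be measured using a self-reported 16-item scale targeting PHN competencies in public health policy". A 19-item scale on the necessity of healthcare activities is secondary, and 29 knowledge and skills questions are third. The feasibility measures are in a section of their own: "We will assess the feasibility of this study based on the recruitment rate, dropout rate, and data completion rate". They have numerical criteria but no rank.

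**Analysis.** The Statistical analysis section applies the Mann-Whitney and chi-square/Fisher tests to baseline differences and primary outcomes, with "values < .05 indicating statistically significant intergroup differences". It then claims power of at least .80 at d=.30. The Sample size section says that no power analysis was done and arrives at 14 nurses from an expected participation rate.

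**The concern.** The primary outcome tells a reader which result is the trial's main finding. Here that is a between-arm test on a self-reported scale in about 14 people, while the measures that decide whether a definitive trial can go ahead are not ranked.

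The stated power makes this worse. A reader who believes the test had power of .80 or more at d=.30 will take a non-significant result as evidence against the program. If the true effect is near .30, a significant result would have to come from an observed difference several times larger, and it would be read as efficacy. Either reading could draw attention from the feasibility findings that are meant to prepare the definitive trial.

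**Working it through.** **Inputs**
- About 600 nurses in the prefecture and a participation rate of 2.4% (Sample size).
- 1:1 allocation (Trial design and settings).
- d=.30, alpha .05, claimed power of at least .80 (Statistical analysis).
- A 50% figure in the dropout and completion criteria; the wording leaves open whether it covers dropout, completion or both (Assessment of the trial feasibility).
- Assumption: two-sided testing, since sidedness is not stated.

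**1. Planned size.** 600 × 0.024 = 14.4, so the protocol's 14 reproduces: 7 per arm.

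**2. Power at the protocol's effect size.** Two-sample t-test, n=7 per arm, 12 degrees of freedom, noncentrality = d × √(n/2), critical value 2.179.
- d=.30: noncentrality 0.30 × √3.5 = 0.561; power 8.1%.
- d=.50: noncentrality 0.935; power 13.9%.
- d=1.0: power 41%.
- d=1.2: power 54%.
- d=1.63: power 80%.

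A simulated exact Mann-Whitney test at 7 v 7 and d=.30 gives about 6%. The claimed .80 does not reproduce.

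**3. Other readings that might rescue the claim** (normal approximation)
- One-sided test, 7 per arm: 13.9%.
- The block description read as six blocks of four, so 24 nurses (12 per arm): 11%.
- 0.30 read as a correlation (d=0.63): 22%.
- 0.30 read as f, as w or as a paired d on all 14: 20%; one-sided paired: 30%.

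None comes near 80%. The size needed at d=.30 is 2 × (1.960 + 0.842)² / 0.30² = 174.4, so 175 per arm or 350 in total, before dropout.

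**4. Precision.** 95% CI half-width for the arm difference, in SD units: 2.179 × √(2/7) = 2.179 × 0.5345 = 1.16. This is nearly four times the assumed effect of 0.30.

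**5. If half drop out.** Seven completers, split 4 v 3. With complete separation of the arms, the smallest two-sided exact Mann-Whitney p is 2 / C(7,3) = 2/35 = .057. With the asymptotic test on the same data, U=12, mean 6 and variance 4 × 3 × 8 / 12 = 8:
- without continuity correction, z = 6/2.828 = 2.12, p = .034;
- with continuity correction, z = 5.5/2.828 = 1.94, p = .052.

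**6. What the feasibility measures would give.** 14 of 600 is 2.3% (exact 95% CI 1.3% to 3.9%). 7 of 14 completing is 50% (23% to 77%). These intervals are wide, but they concern the question that the trial is set up to answer.

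**The case against.** The strongest defence is that preliminary effect is a declared co-aim. The Background, the section on preliminary effects and the Discussion all name it, and collecting scale data to size the definitive trial is an explicit purpose. A reader might infer from the limitations that the trial disowns effects altogether; the document as a whole does not support that. This part of the objection stands: the defect is inconsistent objectives. It does not rescue the ranking or the test, because preliminary effects and sample-size inputs can be reported as estimates with intervals.

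Three other strong readings also go too far.
- **That p<.05 can never be reached.** This needs 50% dropout, an analysis of completers only and an exact two-sided Mann-Whitney test. The 50% criterion is unclear, the plan states intention-to-treat, and it does not call for an exact Mann-Whitney test. The uncorrected asymptotic p is .034.
- **That non-significance is nearly certain.** About 92% of such trials would be non-significant at d=.30, but power is 41% at d=1.0. The protocol gives no observed effect for this program.
- **That all three scales are certain to be tested at p<.05.** The sentence on between-arm tests names only primary outcomes. The other two scales are reached through general wording.

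It is also fair to say that feasibility has its own criteria, comes first in the analysis section and is the stated conclusion. Its displacement is therefore a risk and not a certainty. What remains is that it has no rank, beside a primary test with a false power statement.

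**Conclusion.** The concern holds in this form. The objective is stated inconsistently, the primary outcome is a competency scale with a between-arm test at p<.05, and the feasibility criteria are unranked. At 7 per arm, power at the protocol's own d=.30 is about 8% against a claimed .80 or more, and the interval is about ±1.16 SD. A significance verdict on this outcome is therefore uninformative at that effect size.

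The figures rest on 14 nurses split equally, two-sided testing and a t-test approximation. The conclusion does not depend on these choices: the highest power under any reading tried was 30%. The point about 50% dropout is conditional and is not needed for the verdict. The collected data stay usable; what needs to change is the inference planned from them.

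**What to change.** 1. State one objective consistently in the abstract, Background, Discussion and Conclusions: feasibility first, with preliminary effects and sample-size inputs as supporting aims.
2. Name recruitment, dropout and data completion as the primary outcomes. Give dropout and completion separate, unambiguous criteria. Settle the rounding of the recruitment criterion too, since the planned 14 of 600 is 2.33%, just under 2.4%.
3. Keep all three scales as exploratory outcomes, reported as between-arm differences with 95% confidence intervals and no p<.05 verdict.
4. Delete the sentence claiming power of at least .80 at d=.30.
5. Carry the ranking into the abstract's Methods, the three outcome sections, the Statistical analysis section and the registry entry. The registry record was not available for this review, so its current ranking is unchecked.
6. Date and disclose the re-ranking. The Trial status section gives registration on March 23, 2021 and the end of recruitment on June 30, 2021, so this is a change of primary outcome after registration and enrolment and must be reported as one.

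**Cost.** No new data are needed. The price is a documented change of primary outcome, which needs a stated reason so that it is not mistaken for outcome switching, and giving up any claim of a significant competency gain.

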#### The necessity of healthcare activities

The secondary outcome will be measured using a self-reported 19-item scale designed to reveal information about the necessity of healthcare activities that are based on evidence and the promotion of decision-making with superiors as a way to improve planning [34]. This scale was confirmed as reliable and valid for use in Japan and is only available in Japanese. The 19 items listed in the scale are organized within four dimensions as follows: (1) three items measured the existence of health needs, (2) five items measure the necessity of addressing health needs based on evidence, (3) five items measure actual conditions that require solutions, and (4) six items measure priorities for resolution. All items will be measured using a 6-point Likert scale: 0 (never applicable), 1 (20% applicable), 2 (40% applicable), 3 (60% applicable), 4 (80% applicable), and 5 (100% applicable).

#### Knowledge, skills, and perspectives of PHNs involved in local healthcare planning

The third outcome will be measured based on 29 questions targeting the knowledge, skills, and perspectives of PHNs involved in local healthcare planning. All items will be measured using a 4-point Likert scale: 1 (never), 2 (not much), 3 (a little), and 4 (a lot).

### Preliminary effects

We will expect the trial to improve relevant competencies among PHNs measured as three outcomes.

### Assessment of the trial feasibility

We will assess the feasibility of this study based on the recruitment rate, dropout rate, and data completion rate. We will set the corresponding criteria to assess the success of feasibility; the recruitment rate will be 2.4%, the dropout rate, and the data completion rate will be 50% based on the previous pilot study [12]. We also will ask the participants for their feedback on the feasibility of the trial and web-based learning self-learning program, clarifying areas that need improvement and/or continual refinement as open-ended survey questions.

### Statistical analysis

We will conduct descriptive statistics (e.g., recruitment rate, dropout rate, and data completion rate) to assess the feasibility of this study and analyze intergroup baseline differences in the data and primary outcomes using the Mann-Whitney *U*-test and the chi-square/Fisher exact test. We will assess whether previous experience in local healthcare planning and other factors affected the study outcomes based on the results of the Mann-Whitney *U*-test and the chi-square/Fisher exact test. Analyses will be performed according to the intention-to-treat principle. We will use IBM SPSS for Windows (version 25; IBM Corp, Armonk, NY, USA) for the analysis and *p*-values < .05 indicating statistically significant intergroup differences. This study is expected to have a power ≥.80 and α ≤.05, assuming a medium effect size (*d* = .30) [35].

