### Sample size

The sample size has not yet been calculated using a power analysis due to feasibility and a limited research budget [29]. However, a rationale for numbers in the pilot trial should be included for pilot studies [30]. Based on our previous RCT, we estimate the participation rate would be approximately 2.4% [17]. In this pilot study, we will focus on a prefecture in the Kanto region in Japan, which has approximately 600 PHNs and 1,930,000 residents. Therefore, we will estimate that 14 PHNs were necessary for this study. Owing to ethical considerations, we do not over-recruit the participants. Further, we expect the participant pool to be limited due to the COVID-19 pandemic, which has resulted in a general shortage of PHNs because most will be involved in frontline activities [28].

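### The only stated between-arm method is a Mann-Whitney test with no baseline adjustment named, though the primary scale is measured at baseline and the pilot is meant to inform the next sample size

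*Protocol article*

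**What the plan says.** The primary outcome is a sum-type questionnaire: "The primary outcome will be measured using a self-reported 16-item scale targeting PHN competencies in public health policy", with each item scored 0 to 3, so 0 to 48 if summed. Under Outcomes and data collection, participants "will complete the outcome scales at the baseline and post-intervention". Every participant who completes the trial therefore has a baseline and a post-test value on the same scale.

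The Statistical analysis section names these methods:
- Feasibility: "We will conduct descriptive statistics (e.g., recruitment rate, dropout rate, and data completion rate) to assess the feasibility of this study".
- Arms: the team will "analyze intergroup baseline differences in the data and primary outcomes using the Mann-Whitney" U-test, with chi-square or Fisher tests for categorical data, at p < .05.
- Other factors: "We will assess whether previous experience in local healthcare planning and other factors affected the study outcomes based on the results of the Mann-Whitney" procedure, together with the same categorical tests.

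No model with a covariate, effect estimate, interval, SD or baseline-post correlation is mentioned. The text does not say whether the outcome test uses post-test scores or change scores.

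The Background gives the purpose of the outcome data: the study will examine preliminary effects, "thus providing relevant data for calculating the sample size needed to conduct a future definitive RCT". The Discussion repeats that aim. On size, the Sample size section says "we will estimate that 14 PHNs were necessary for this study", which is 7 per arm at 1:1.

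**The concern.** Three things do not fit together.

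1. **The baseline score is collected but has no stated role in estimating the effect.** Its only stated use is in a test of whether the arms differ at baseline. After randomisation any such difference is due to chance, so the test answers no useful question. With 7 per arm it would also miss most large imbalances. A comparison of post-test scores alone carries a chance imbalance forward in proportion to the baseline-post correlation.

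2. **The chosen output does not match the aim.** A Mann-Whitney test returns a U statistic and a p-value. Sizing a trial on this scale needs an SD and, if the definitive analysis adjusts for baseline, the baseline-post correlation.

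3. **A p < .05 test is the wrong summary for about 14 people.** An estimate with its interval shows how little is known; a non-significant rank test does not.

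At stake are the usefulness of the pilot's outcome data for the next design and, if the correlation is high enough, some precision.

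**Working it through.** **Sample size.** The Sample size section says "we estimate the participation rate would be approximately 2.4"%, applied to about 600 nurses: 600 × 0.024 = 14.4. The stated 14 reproduces.

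**Stated power.** The Statistical analysis section expects power of at least .80 at d = .30. With 7 per arm and two-sided .05, the t-test has 8.1%; 80% needs 175 per arm by the normal approximation. The stated power does not reproduce. That is a separate error, but it sets the scale for what follows.

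**Chance baseline imbalance.** In SD units the SE of a difference in means is √(2/7) = 0.535. P(|difference| > 0.5 SD) = 2 × [1 − Φ(0.5/0.535)] = 2 × [1 − Φ(0.935)] = 0.35. At r = .5, a 0.5 SD imbalance shifts the expected post-test difference by 0.5 × 0.5 = 0.25 SD.

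**Precision with 7 per arm.** The correlation r is not in the document, so a range is assumed. For large samples, adjustment (ANCOVA) multiplies the variance by 1 − r². In small samples there is a further cost from the lost degree of freedom and from estimating the slope. Approximate half-widths are:
- unadjusted: t(12 df) × 0.535 = 2.179 × 0.535 = 1.16 SD;
- adjusted: t(11 df) × 0.535 × √(1 − r²) × √(1 + 1/10), with t = 2.201.

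Simulated values (normal data) are mean half-widths. They run slightly lower because the SD is estimated.

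| r (assumed) | 1 − r² | Adjusted, formula | Adjusted, simulated | Unadjusted, simulated |
|---|---|---|---|---|
| .3 | .91 | 1.18 | 1.15 | 1.14 |
| .5 | .75 | 1.07 | 1.04 | 1.14 |
| .7 | .51 | 0.88 | 0.86 | 1.14 |

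There is no gain at r = .3 and a clear one only from about r = .5.

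**If change scores were meant.** Their variance factor is 2(1 − r). The ratio of ANCOVA to change-score variance is (1 − r²)/[2(1 − r)] = (1 + r)/2, which is .75 at r = .5 and .85 at r = .7. ANCOVA is still the more precise in large samples, by a smaller margin at r = .7.

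**If only half complete.** The feasibility section sets 50% for data completion, which gives about 7 people, say 3 v 4. Simulated half-widths, unadjusted v adjusted, are 1.86 v 2.13 (r = .3), 1.86 v 1.95 (r = .5) and 1.86 v 1.62 (r = .7). The crossover lies near r = .6. At 3 v 4 there are C(7,3) = 35 allocations, so the smallest two-sided exact Mann-Whitney p is 2/35 = .057. The stated threshold could not be reached whatever the data.

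**Power at the plan's own effect, d = .30, 7 per arm (simulated).** Mann-Whitney on post-test scores gives 6-7%. ANCOVA gives 8.4%, 8.9%, 11.3% and 13.3% at r = .3, .5, .7 and .8.

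**Why the correlation matters for the next trial.** At d = .30, 80% power and two-sided .05, n per arm is 175 unadjusted. With ANCOVA it is 175 × (1 − r²), or about 159, 131, 89 and 63 at r = .3, .5, .7 and .8.

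**How well this pilot can supply those inputs.** With 14 complete records, the 95% interval for the SD runs from about 0.72 to 1.65 times the estimate (12 df). An observed r of .5 has an interval of about −.04 to .81.

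**The case against.** The strongest reply is that this is a condensed article about a pilot whose Discussion puts feasibility ahead of effectiveness. For about 14 people on a bounded ordinal sum score, a rank test is a cautious and defensible choice. Naming it does not stop the team from reporting SDs or correlations, and a fuller analysis plan may list them. Much of this stands, and it limits the point in four ways.

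- A reader might infer that the plan yields none of the inputs a definitive trial needs. It does not say that. Recruitment, dropout and completion rates are planned and are such inputs, and they are given as examples, so score summaries are not excluded. The gap is in what the named test itself delivers.
- A reader might infer that the comparison is certainly unadjusted. That is the natural reading, but change scores are not ruled out, and the sentence runs baseline and outcome comparisons together.
- A reader might infer that adjustment would greatly raise power. With a large effect chosen for illustration (d = 1.0, not the document's), simulated power at r = .5 is .34 for Mann-Whitney, .40 for an unadjusted t-test and .475 for ANCOVA. Nearly half of that rise comes from replacing a discrete rank test, not from using the baseline.
- The simulations assume normal data, which favours ANCOVA, and at 50% completion adjustment can widen the interval.

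The feasibility argument does not remove the point. The plan still tests outcomes between arms at p < .05 and still promises data for sizing the next trial. The article states its method, so this concerns a choice made rather than a detail left out. The objection to baseline tests is sound but minor, since no decision is tied to them.

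**Conclusion.** The point holds in limited form. The primary scale is measured twice, but the only stated between-arm method is a Mann-Whitney test with no baseline adjustment named, accompanied by uninformative baseline significance tests. That test does not itself supply the effect with interval, SD or correlation that the sample-size aim calls for.

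The main benefit of a change is output that suits the pilot's purpose. The precision gain is conditional on a correlation that the document does not give: none at r = .3, about 9% off the half-width at r = .5 (1.04/1.14) and about 25% at r = .7 (0.86/1.14). These figures assume normal data and all 14 completing. The documents do not support a claim that precision is certainly being wasted, or that adjustment would rescue power.

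**What to change.** In the Statistical analysis section:

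1. Make the main outcome summary the baseline-adjusted mean difference, from a linear model of the post-test total on arm and baseline total, with a 95% CI.
2. Show the unadjusted difference with its CI alongside, because adjustment may lose precision if few complete or the correlation is low.
3. Report the SD per arm, the residual SD and the baseline-post correlation, each with an interval, as planning inputs that are imprecise at this size.
4. Keep Mann-Whitney as a sensitivity analysis and say whether it uses post-test or change scores.
5. Present baseline data descriptively by arm, without p-values.

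The cost is a few lines of wording and no new data. The adjusted model spends one degree of freedom and assumes linearity on a bounded 0-48 score. With about 7 completers it widens the interval unless r is about .6 or more.
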